## Abstract

**Background:**

Tuberculosis is a major public health concern resulting in high rates of morbidity and mortality worldwide, particularly in low- and middle-income countries. Tuberculosis requires a long and intensive course of treatment. Thus, various approaches, including patient empowerment, education and counselling sessions, and involvement of family members and community workers, have been suggested for improving treatment adherence and outcome. The current randomized controlled trial aims to evaluate the effectiveness over usual care of an innovative multicomponent people-centered tuberculosis-care strategy in Armenia.

**Methods/design:**

Innovative Approach to Tuberculosis care in Armenia is an open-label, stratified cluster randomized controlled trial with two parallel arms. Tuberculosis outpatient centers are the clusters assigned to intervention and control arms. Drug-sensitive tuberculosis patients in the continuation phase of treatment in the intervention arm and their family members participate in a short educational and counselling session to raise their knowledge, decrease tuberculosis-related stigma, and enhance treatment adherence. Patients receive the required medications for one week during the weekly visits to the tuberculosis outpatient centers. Additionally, patients receive daily Short Message Service (SMS) reminders to take their medications and daily phone calls to assure adherence and monitoring of treatment potential side effects. Control-arm patients follow the World Health Organization - recommended directly observed treatment strategy, including daily visits to tuberculosis outpatient centers for drug-intake. The primary outcome is physician-reported treatment outcome. Patients’ knowledge, depression, quality of life, within-family tuberculosis-related stigma, family social support, and self-reported adherence to tuberculosis treatment are secondary outcomes.

**Discussion:**

Improved adherence and tuberculosis treatment outcomes can strengthen tuberculosis control and thereby forestall tuberculosis and multidrug resistant tuberculosis epidemics. Positive findings on effectiveness of this innovative tuberculosis treatment people-centered approach will support its adoption in countries with similar healthcare and economic profiles.

**Trial registration:**

ClinicalTrials.gov registration number: NCT02082340. Date of registration: 4 March 2014.

## Background

Tuberculosis (TB) is an airborne infectious disease transmitted from person to person, and is a major public health concern [1]. In 2012, TB affected more than 8.6 million people worldwide and resulted in 1.3 million deaths, which made it second only to HIV among leading causes of infectious disease-related deaths [1]. More than 80 % of active TB cases in the world are concentrated in 22 low- and middle-income countries [2], where 95 % of all TB deaths occur [3]. Moreover, TB is the leading cause of death among HIV patients, accounting for 20 % of all causes of deaths among HIV-infected people [2].

Drug-sensitive strains of TB are treated with four standard first-line anti-TB drugs. Non-compliance to treatment, misuse, or mismanagement of medications may lead to relapse, development of drug-resistant (DR) TB (which requires a more expensive and intensive treatment course), and even death [4, 5]. According to the 2013 World Health Organization (WHO) progress report [1], each year an estimated 450,000 cases and 150,000 deaths occur globally due to multidrug-resistant TB (MDR-TB). According to 2012 WHO data, 3.6 % of all new TB cases were MDR-TB, while the rates among previously treated patients reached 20 % [6]. Among those with MDR-TB, approximately 9.6 % suffer from extensively drug-resistant (XDR) strains. In addition to these adverse health consequences, TB places a tremendous economic burden on individuals and societies [7].

### Current treatment approaches and alternative strategies

Currently, WHO recommends directly observed therapy (DOT) to monitor patients’ adherence to the treatment regimen, with an optimal dosing frequency of 6 days per week for new TB patients. In DOT, patients take their medications while being observed by a healthcare worker, usually a physician or a nurse [8]. DOT prevents patients from missing their treatment and thus reduces the development of resistance. The outpatient phase of DOT, requiring near daily visits to the health facility, introduces significant financial and time-related costs to patients [9], particularly in areas with poor access to health services [10]. Given such limitations, researchers have implemented and evaluated various modified or alternative strategies to improve patients’ adherence to TB treatment [5, 11–14]. A systematic review of randomized controlled trials did not suggest enough evidence that DOT compared to self-administered treatment leads to better treatment outcomes in people receiving treatment in low-, middle-, and high-income countries [5].

Empowering patients is recommended as one of key components of TB treatment [15]. Although several authors have documented the effectiveness of patient empowerment in TB treatment [16–19], as identified in a review by Macq *et al.* in 2007 [20], people-centered solutions have received less attention globally. In low-resource countries, as an alternative to traditional DOT, researchers have recruited family members to observe patients’ medication intake, making treatment easier and less expensive [10, 21]. Family members are interested in identifying noncompliance and motivated to encourage and promote treatment adherence. Several studies [10, 21, 22] have documented the effectiveness of involving family members in TB treatment. Some patients value family involvement, especially if the observer is a family decision maker or is highly respected in the family [23]. Moreover, WHO has encouraged the development of innovative people-centered care strategies that, where medically appropriate, enable patient self-management and community engagement to improve health outcomes [24, 25].

In recent years, the widespread availability of mobile phones [26] has spawned numerous health communications interventions [27–29]. The Short Message Service (SMS) has been widely used as a reminder for patients to take their medications and improve treatment adherence [27–29]. Although, SMS reminders have shown significant improvement in medication adherence among patients with HIV [27], asthma [30], and other conditions, a recent review paper evaluating the effectiveness of SMS reminders for treatment adherence among TB patient was inconclusive, identifying methodological limitations of prior studies and suggesting further controlled trials evaluating the role of SMS reminders for TB adherence [31].

Patient counseling and education have been found to improve treatment adherence among TB patients [11, 32], which in turn, results in better treatment outcomes and improvement in the patients’ quality of life [33].

Treatment adherence has been associated with many different factors [9], including social support, healthcare satisfaction, and disease-related knowledge. Multicomponent interventions were found to improve treatment adherence [34]. Hence, our team developed a multicomponent innovative approach to TB care to enable self-administered drug intake by empowered TB patients - supervised by a trained family member and supported by patient and family counseling and reminders - to improve treatment adherence and outcome, and thereby forestall TB and multidrug resistant TB epidemics. The innovative treatment approach integrates several educational, technological, and social evidence-based components.

### Aims and objectives

The current randomized controlled trial aims to evaluate the effectiveness of an alternative multicomponent TB outpatient care strategy consisting of the following: 1) education and counseling for drug-sensitive TB patients and their family members, 2) self-administered drug-intake supervised by a trained family member, 3) daily SMS reminders to TB patients, and 4) daily phone calls to supporting family members. The research team is measuring if this alternative TB care strategy offers advantages over the regular DOT in terms of treatment outcomes, patients’ and family members’ knowledge about TB, patients’ depression status and quality of life, TB-related stigma, family social support, and self-reported adherence to TB treatment.

## Methods/design

### Trial design

This is an open-label, stratified cluster randomized controlled superiority trial with two parallel equal arms (intervention and control) conducted in Armenia. TB outpatient centers defined the clusters, with equal numbers of clusters assigned to intervention and control arms. We performed a cluster-level random assignment of drug sensitive TB patients to intervention and control arms to mitigate potential contamination of participants in the control arm.

### Study setting and eligibility criteria for clusters

The intervention takes place during the continuation phase of TB treatment and is implemented through Armenia’s TB outpatient centers. TB centers having a minimum patient load of five drug-sensitive TB patients in 2012 were included to ensure that centers with very small patient loads did not decrease the study’s power. Out of 60 TB outpatient centers in Armenia, 52 met the inclusion criterion.

### Eligibility criteria for individual tuberculosis patients

Study participants are patients starting their continuation phase of TB treatment in selected outpatient TB care centers. The patient eligibility criteria are as follows:Having a diagnosis of drug sensitive pulmonary TB,Starting the continuation phase of TB treatment between March and-December 2014,Being at least 18 years old at the time of enrolment, andThe ability to communicate in Armenian.

The eligibility status of each patient is subject to verification by the corresponding TB outpatient center physician and the psychologist of the National Tuberculosis Control Center (NTC).

### Assignment of intervention/randomization

We stratified the TB outpatient centers (clusters) based on their drug-sensitive patient load in 2012 and their treatment outcomes (performance). We classified TB outpatient centers as small, average, or large, and performance outcomes as below average, average, or above average, yielding nine distinctive cluster categories. We applied computer-assisted block randomization to assure relatively equal number of cluster representatives from each of these nine categories in the intervention and control arms. The process yielded 26 centers in each arm.

### Cluster level interventions

TB physicians in both intervention and control clusters are instructed and requested to inform the study team whenever they have a patient who meets the inclusion criteria. In addition, all TB physicians and nurses in the intervention clusters are trained on the study protocols and procedures. They are instructed to closely follow the study protocols and perform study-related paper work, including the distribution and collection of weekly side effect and medication intake forms (applicable only to intervention clusters). Physicians in the intervention clusters also are trained to provide patients with a one-week supply (6 days of pills) of TB medications using the designated pillboxes.

### Individual level interventions

Patients in the intervention arm are asked to identify a family member to provide support during the course of treatment. The patients, their supportive family member, and other interested family members, as permitted by the patient, participate in TB educational and psychological counseling session provided by a team of a psychologist and a nurse (interventionists).

The interventionists participated in a training-of-trainers course before starting fieldwork. The interactive TB educational and psychological counseling session covers various topics, including TB symptoms, TB route of transmission, TB treatment strategies, importance of treatment adherence, prevention and infection control, handling side effects, addressing TB-related stigma and common myths. Average duration of each session is approximately 90 minutes. The primary objective is to empower TB patients and their family members to take responsibility for the treatment.

After the educational and counseling session, patients visit their physicians weekly in the TB outpatient centers for a medical check-up and to receive the prescribed TB medication for that week. The supportive family members are responsible for following the TB patients and supporting their adherence to the treatment regimen. The supportive family members also are responsible for completing a form each week documenting medication intake and observed side effects. Patients return the completed form to the TB physician during the next week’s visit.

Patients receive daily SMS messages each morning reminding them to take their medications on time, and weekly SMS messages reminding them to visit their TB physician for their weekly supply. The supportive family members receive daily phone calls from the research team each evening to inquire about side effects related to TB medication and to inquire if the patients are taking their TB medications on a timely basis. During these calls, patients and family members also are offered additional psychological advice and support if needed.

Patients in the intervention arm who lack a supporting family member also assume all the responsibilities defined for the supportive family member.

Patients in the control arm follow the regular DOT strategy for continuation phase, in line with the guidelines of Armenia’s Ministry of Health and WHO recommendations: it includes taking prescribed TB medication 6 days per week while being observed by a health-care provider. The patients in this group do not receive any additional intervention.

### Outcomes and additional measurements

The primary outcome of this controlled trial is TB treatment outcome according to WHO definitions as recorded in the medical file and reported to the NTC. Treatment outcomes are classified as follows: cured, completed treatment, dead, failed, defaulted, and transferred [35]. A patient is considered to be successfully treated if he/she has a cured or completed treatment outcome. All other categories are considered as an unsuccessful treatment outcome.

Secondary outcome measures include patients’ knowledge, depression status, quality of life, within-family TB-related stigma, family social support, and self-reported adherence to TB treatment. In addition, we measure family members’ knowledge, depression status, social support toward TB patient, and TB-related stigma. All the secondary outcomes other than self-reported treatment adherence are measured at T0 (baseline) and T1 (follow-up). Self-reported treatment adherence is assessed only at T1. The knowledge variable is constructed from correct responses to five items adapted from previous work [36–38]. Depression is assessed using a modified version of the Center for Epidemiological Studies Depression (CES-D) scale [39]; the Armenian translation is validated and the negatively formulated 16 items show high diagnostic accuracy and good factorial structure [40, 41]. We have used a modified version of a validated scale to measure within-family TB related stigma [42] and the Berlin social support scale [43] to measure social support of family members toward TB patients. We have applied EQ-5D to obtain data on quality of life of patients [44].

Measurements on sociodemographic characteristics including age, gender, socioeconomic status, education, marital status, and health behavior (smoking and drinking) are obtained to verify the validity of randomization and, if necessary, to control for the potentially confounding effects of these variables on the primary and secondary outcomes. Table 1 summarizes the study outcomes and presents the frequency of data collection.

**Table 1 Tab1:** Outcome variables

			Timeline	
Variable	Source	Type	T0^a^	T1^b^
Treatment outcomes	National Tuberculosis Control Center reported treatment outcome evaluation	Categorical		X
Possible Depression	Patient survey	Continues	X	X
Quality of life	Patient survey	Continues	X	X
TB knowledge	Patient survey	Continues	X	X
TB-related stigma within family	Patient survey	Continues	X	X
Social support	Patient survey	Continues	X	X
Treatment adherence	Patient survey	Ordinal		X
Possible depression	Family member survey	Continues	X	X
TB knowledge	Family member survey	Continues	X	X
TB-related stigma	Family member survey	Continues	X	X
Social support	Family member survey	Continues	X	X

^a^At the beginning of continuation phase of treatment/before intervention

^b^After completion of continuation phase of TB treatment

*TB*, tuberculosis

Baseline and follow-up surveys are interviewer-administered. Given the characteristics of the intervention protocol, blinding interviewers assessing secondary outcomes (knowledge about TB, depression, quality of life, within-family TB-related stigma, and family social support) at baseline is not possible. However, interviewers are blinded for the assessment of secondary outcomes at follow-up. The treatment outcome (primary outcome variable of interest) is assessed and reported by the corresponding TB outpatient center physician as part of regular reporting to the NTC; this process is completely independent of the research team.

### Recruitment

The NTC informed physicians and nurses in all 52 eligible TB outpatient centers (clusters) of the study and invited them to be involved in the trial. All agreed to participate. Health-care workers in the intervention and control clusters are instructed and requested to report on all new and previously treated drug sensitive TB patients who start their continuation phase of TB treatment in the selected TB outpatient centers. The NTC psychologist, who had special training on the protocols and procedures of this study, makes the initial contact with the eligible patients following these steps: 1) the TB physicians report eligible patients to NTC, 2) the NTC psychologist contacts eligible patients over the phone, 3) the NTC psychologist verifies patients’ eligibility, 4) the NTC psychologist presents the study information briefly in a phone call and gets the patients’ consent to share their contact information with the research team, and 5) the NTC psychologist schedules a face-to-face meeting between the TB patient and the research team members.

The NTC psychologist also asks patients about household size and the number of family members aware of the TB diagnosis. If it becomes evident that all members of the patient’s family know about his/her disease and if the patient expresses desire for family members to receive TB counseling, then the NTC psychologist arranges an appropriate place (usually home of the patient), date and time for the counseling session. We ask the patients to identify potential supporters from their family members who participate in the counseling session to support them during their treatment period. If the patient lives alone or is unwilling for any family member to support him/her during the treatment and to participate in the counseling session, we set a convenient place (usually TB outpatient center), date and time for the TB patient’s counseling session.

Patients are enrolled within 15 days from the start of their continuation phase of treatment. The average duration of the continuation phase for the drug sensitive TB treatment is about four months. We anticipate completion of recruitment and data collection within 12 months from the start of the field work.

### Sample size

We based sample size calculations for this study on the treatment outcome as the main variable of interest. In 2012, 1,200 drug sensitive TB patients received the continuation phase of their treatment in TB outpatient centers. Utilizing the 2012 data on the number of patients and outcomes at each TB outpatient center, we identified 52 eligible clusters from the 60 centers. We calculated the intracluster correlation to be 0.04 and estimated the design effect as 1.6 [45]. The initial sample size calculation used a 10 % difference in the primary outcome [38], an alpha of 0.05 and power of 80 % and yielded a sample size of 95. Considering the potential for losses to follow-up taking a more conservative approach, we used a design effect of two; thus, the required sample size was calculated to be 190 in each arm.

### Data collection

We utilize interviewer-administered face-to-face surveys to collect data on secondary outcomes. All patients and their family supporters (if any) in the intervention and control arms are asked to complete an interviewer-administered questionnaire at baseline (T0) and after completion of their TB treatment (T1, follow-up).

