### Statistical analyses

Statistical analyses will follow the intention-to-treat principle [46]. We will assess randomization across the two arms by comparing sociodemographic characteristics and other potential confounding variables using chi-square for binary and categorical variables, t-test, or other equivalent nonparametric tests, as appropriate, for continuous variables.

The primary outcome (treatment outcome) will be analyzed using generalized mixed effect model applying binomial distribution, logistic regression [47]. The status of randomization (intervention/control) will be included as an independent variable; to account for the clustered design we will treat clusters as a random effect. Potential confounding variables (age, gender, socioeconomic status, and others) with significant differences across intervention and control arms will be included as fixed factors. Secondary outcomes including knowledge, depression status, quality of life, within family TB-related stigma, and family social support also will be tested using generalized linear mixed effect models using logistic regression or linear regression, as appropriate. The secondary outcome model also will include its baseline assessment as a covariate.

We will report all the descriptive and inferential statistics results with their 95 % confidence intervals.

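### The follow-up survey (T1) is timed only by completion of treatment, so patients who stop early have no survey time, which risks arm-dependent selection in the secondary outcomes, chiefly self-reported adherence

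*Protocol article*

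**What the plan says.** The article defines T1 in two places. Under Data collection, patients and supporters answer the second questionnaire "after completion of their TB treatment (T1, follow-up". Table 1, footnote b, under Outcomes and additional measurements, puts it as "After completion of continuation phase of TB treatment". Neither place gives a calendar time, a window, or an alternative for a patient who does not complete. T0, by contrast, is tied to the start of the continuation phase, with enrolment within 15 days of that start (Recruitment).

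On who is surveyed, Data collection is inclusive: "All patients and their family supporters (if any) in the intervention and control arms are asked to complete an interviewer-administered questionnaire".

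On what is surveyed, the Outcomes section says "All the secondary outcomes other than self-reported treatment adherence are measured at T0 (baseline) and T1 (follow-up", and then "Self-reported treatment adherence is assessed only at T1".

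The primary outcome has the categories "cured, completed treatment, dead, failed, defaulted, and transferred". A patient counts as "successfully treated if he/she has a cured or completed treatment outcome". It is taken from the medical file and NTC reporting, not from the survey.

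Under Statistical analyses: "Statistical analyses will follow the intention-to-treat principle". Secondary-outcome models are to include the baseline value as a covariate.

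**The concern.** Completion happens after randomisation, and it overlaps with one of the two success categories of the primary outcome. A patient who defaults does not reach it, so the instruction to survey that patient has no time at which it can be carried out. Field staff must then either improvise a date or leave the interview undone.

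The intervention is meant to improve adherence and treatment outcome. If it works, more of its patients reach T1 than in the control arm, and the patients it has kept on treatment may be weaker adherers than those who would have finished anyway. A comparison of surveyed patients would then compare two differently selected groups.

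Adherence is the worst placed of the secondary outcomes. It has no T0 value, so the planned baseline adjustment cannot help. The daily-call data and the weekly intake forms exist only in the intervention arm and cannot fill the gap for controls.

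**Working it through.** **Inputs from the article (Sample size; Recruitment):** planned difference 10 percentage points; 190 per arm; estimated design effect 1.6, with 2 used; average continuation phase about four months. The control success rate, the sidedness of the test and the expected share of missed T1 interviews are not given.

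**1. The plan's own figure.** 95 x 2 = 190 per arm, as stated. The 95 cannot be verified without a control rate. With a two-sided 0.05 test, 80% power and no continuity correction, a 10-point difference needs 199 per arm at 80% vs 90%, 102 at 88% vs 98%, and 88 at 89% vs 99%. So 95 per arm corresponds to roughly 88.5% vs 98.5%. A one-sided test would put the control rate near 87%, and a continuity-corrected two-sided test near 90%. The shift in step 2 does not depend on which rate was used.

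**2. Shift of a survey mean.** Let p be the share observed at T1 in an arm and g the gap in mean between observed and unobserved patients.

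- Observed mean minus all-patient mean = (1 - p) x g.
- Shift in the arm contrast, with the same g in both arms = (1 - p1) x g - (1 - p0) x g = -(p1 - p0) x g.
- Upper case, with every unsuccessful patient unobserved: p1 - p0 = 0.10, so the shift is -0.10 x g.
- With g = 1 SD (assumed), the shift is 0.10 SD against the intervention; with g = 0.5 SD it is 0.05 SD.

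**3. Number of patients, of 190 per arm, in that upper case (success rates assumed).**

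| Control vs intervention success | Unsuccessful, control | Unsuccessful, intervention |
|---|---|---|
| 88.5% vs 98.5% | 0.115 x 190 = about 22 | 0.015 x 190 = about 3 |
| 80% vs 90% | 0.20 x 190 = 38 | 0.10 x 190 = 19 |
| 70% vs 80% | 0.30 x 190 = 57 | 0.20 x 190 = 38 |

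**4. Adherence as a proportion (all rates assumed; completion 80% vs 90%).**

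- If 90% of completers and 20% of non-completers adhere in both arms, the all-patient figures are 0.80 x 0.90 + 0.20 x 0.20 = 0.76 and 0.90 x 0.90 + 0.10 x 0.20 = 0.83. The true difference is 7 points. A survey of completers alone shows 90% vs 90%, a difference of 0.
- With 40% adherence in non-completers, the all-patient figures are 0.72 + 0.08 = 0.80 and 0.81 + 0.04 = 0.85. The true difference is 5 points, and completers alone again show 0.
- Suppose the extra 10% who finish under the intervention are 60% adherent, and non-completers 20%. Completers alone give (0.80 x 0.90 + 0.10 x 0.60) / 0.90 = 86.7% for the intervention against 90.0% for control. All patients give 0.72 + 0.06 + 0.02 = 80% against 76%. A benefit of 4 points appears as a deficit of about 3.

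**5. Against sampling error.** With 190 per arm, the standard error of a mean difference in SD units is sqrt(2/190) = 0.103, or 0.103 x sqrt(1.6) = 0.13 if the stated design effect also holds for these outcomes. A 0.10 SD shift is somewhat smaller than one standard error.

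**The case against.** The strongest reply is that the article excludes nobody. All patients in both arms are asked, and completion may simply be loose wording for the end of the treatment period. A reader might infer that defaulted, failed and transferred patients are left out by construction. The text does not say so, and this part of the reply stands. What it does not supply is a T1 time for a patient who stops: the sentence that asks everyone also sets the time by completion.

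Completion is also not success. A patient classed as failed may have finished the continuation phase, so it would be too strong to say that the survey is conditioned on the primary outcome. Defaulters are the clear case; transferred and failed patients are only possible ones. Patients who die cannot be interviewed under any timing. The counts above include all of these groups and are therefore upper figures.

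A reader might also see a contradiction with the intention-to-treat statement. Missing survey data do not strictly contradict analysis by assigned arm, although a survey of completers alone would fit that aim poorly.

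On size, the 0.10 SD rests on assumptions, lies below one standard error, and runs against the intervention when the gap is equal in both arms, so in that case it would not create a false benefit. Baseline adjustment may absorb part of it for outcomes with a T0 value. All of this stands, but the last point does not reach adherence. Nor does anything in the article support a claim that nearly all poor adherers would vanish, since a patient can finish the course having missed doses.

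Finally, measuring at the end of treatment is a legitimate way to capture whole-course adherence, and an article commonly leaves tracing procedures, windows and missing-data handling to the full protocol. Their absence is not the point here. The point is the T1 anchor that the article does state, twice, and that has no meaning for patients who stop.

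**Conclusion.** The concern holds as a risk of selection that differs by arm in the survey-based secondary outcomes, most of all self-reported adherence. It is not a stated exclusion of non-completers, and it does not touch the primary outcome.

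For outcomes with a baseline value, the upper-case shift is about 0.10 SD before adjustment, given an assumed 1 SD gap that is equal in both arms. For adherence, the illustrations show that a true benefit of 5 to 7 points could disappear, or one of 4 points could reverse. They rest on assumed completion and adherence rates and on every non-completer being missed. The real size depends on how many patients who stopped are in fact interviewed, which the article does not say. Severity is moderate.

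**What to change.** Define T1 for every enrolled patient and family supporter by a time that does not depend on completion. One option is the scheduled end of the continuation phase, counted from its start (about four months on average by the article's own figure), with a stated window. Attempt the interview with surviving patients who defaulted, failed or transferred, using the same interviewers and questionnaire. State how deaths are handled for these outcomes. Report T1 completion by arm and by treatment outcome, so that readers can judge any remaining selection.

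The cost is a change of wording and modest tracing effort. Some patients with prolonged treatment would be interviewed before they finish, so their adherence report would not cover the whole course; the article gives no distribution of duration from which to say how many. The trial was already enrolling when the article was submitted, so the change would help only patients whose T1 is still to come. Interviews not attempted cannot be recovered at analysis, and for earlier patients the report of T1 completion by arm and outcome is the main safeguard.
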